#### Baseline data and Outcome data

A two-way analysis of covariance (ANCOVA) test will be used to examine the percentage change of inflammatory and non-inflammatory lesions from baseline to the end of the trial when controlling for baseline and other covariates. A repeated measured ANCOVA test will be performed for evaluation of any significant difference in count of inflammatory and non-inflammatory lesions, Skindex-29 score, and VAS score between baseline and the end of the trial. If there is an interaction between KRTE and acupuncture, only the interaction will be shown. If not, the main effect of KRTE and acupuncture will be reanalyzed and presented. According to 'improvement' or 'no-improvement' of IGA score between baseline and the end of the trial, the difference among the groups will be evaluated using a Chi-square test or Fisher's exact test.

Proportion of drop-outs and compliance with KRTE and questionnaire completion will be calculated and described as n (%). The percentage of subjects in each group will be compared using a Chi-square test or Fisher's exact test.

All adverse events reported during the study will be included in the case report forms; the incidence of adverse events will be calculated. The percentage of subjects with adverse events in each group will be calculated and compared using a Chi-square test or Fisher's exact test.

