## Method/Design

### Objective

The aim of this study is to investigate the efficacy and interaction of KRTE in male patients with acne vulgaris and evaluate the feasibility of a large clinical trial.

The null hypothesis is as follows: (1) there is no interaction of KRTE and acupuncture treatment on mean percent change of inflammatory acne lesions between baseline and the end of the trial; (2) mean percent change of inflammatory acne lesions between baseline and the end of the trial is equal in both the KRTE treatment group and the waiting list group; (3) mean percent change of inflammatory acne lesions between baseline and the end of the trial is equal in both the acupuncture treatment group and the waiting list group.

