### Design

This study is a randomized, 2 × 2 factorial, waiting list controlled, assessor single blinded and single-center pilot trial.

The study will be sequentially conducted as follows: enrollment after screening via inclusion and exclusion criteria, randomization, a treatment period of 4 weeks, and assessment (Figure 1).

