### Randomization and blinding

After enrollment, participants will be randomly assigned to the waiting list (WL), acupuncture only (AO), KRTE only (KO), and KRTE combined with acupuncture treatment (KA) groups. The allocation ratio will be 1:1:1:1 in blocks of 4. Randomization will be performed at a site remote from trial location. Random numbers will be generated by a computerized random-number generator through the block-randomization method of a software program (Excel, Microsoft Office 2007) for sequence generation and we will make two separate database: a "patients" database that lists basic information such as patient name, contact details and so on, and a "randomization" database that holds data on which patients have been registered on trial along with their allocations. The "patients" database will be accessible to any researcher whereas the "randomization" database will be password protected so that it will be accessible only by the principal investigator and a nominated statistician [31]. The assessor, who will not be the acupuncture practitioner and KRTE supplier, and who is blinded to the allocation results until the end of study, will perform the outcome assessment.

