#### Secondary outcomes

Secondary outcomes will be shown by the mean percentage change of non-inflammatory lesion counts from baseline to the end of the trial, count of inflammatory and non-inflammatory lesions, the quality-of-life scale (Skindex-29), Visual Analogue Scale (VAS) [score 0 (no symptoms) to 100 (severe symptoms)], and the Investigator Global Assessment [IGA; after evaluation from score 1 (very good) to 5 (very poor) every session, we divided into 'improvement' or 'non-improvement' between baseline and the end of the study]. Skindex 29 will be checked at weeks 0 (baseline) and 4 (end of the trial). VAS and IGA will be checked every session from baseline (just before randomization) and through the 4 weeks after randomization. A Lumix DMC-LX2 digital camera (Panasonic, Osaka, Japan) was used to photograph each patient's face, so that inflammatory and non-inflammatory lesions could be counted at weeks 0 (baseline) and 4 (end of the trial).

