### Statistical methods

#### Statistical analysis plan

Statistical analysis will be conducted on an intension-to-treat basis with a 95% confidence interval using SPSS version 12.0 for Windows. Missing values of drop-out participants will be imputed by the last observation carried forward (LOCF) method. Data will be displayed as the mean ± standard deviation (SD) for continuous data or n (%) for categorical data.

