### Sample size

This study is a pilot study for evaluation the interaction and efficacy of KRTE and acupuncture in male patients with acne vulgaris and the feasibility of a large clinical trial. Because this trial was designed to be of short duration, lasting four weeks, with the intention of decreasing the drop-out rate, the desired sample size for this pilot study is 44 patients, with 11 for each group, assuming a drop-out rate of 10%.

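### The planned four-group test of IGA improvement gives no KRTE effect, acupuncture effect or interaction in a 2 × 2 factorial trial; the repeated-measures ANCOVA for counts and Skindex-29 is a lesser point of precision

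*Protocol article*

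**What the plan says.** The Design section states: "This study is a randomized, 2 × 2 factorial, waiting list controlled, assessor single blinded and single-center pilot trial". The first null hypothesis under Objective, written for the primary outcome, is that "there is no interaction of KRTE and acupuncture treatment on mean percent change of inflammatory acne lesions". The other two concern each treatment against the waiting list.

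The section Baseline data and Outcome data handles the outcomes in three ways:

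- **Percentage change in inflammatory and non-inflammatory lesions:** two-way ANCOVA controlling for baseline and other covariates.
- **Lesion counts, Skindex-29 and VAS:** "A repeated measured ANCOVA test will be performed for evaluation of any significant difference in count of inflammatory and non-inflammatory lesions", and likewise for the two scores, described as a comparison of baseline with the end of the trial. A factorial reporting rule follows: show the interaction if there is one, otherwise the main effects of KRTE and acupuncture.
- **IGA:** the change from baseline is classed as improved or not, and "the difference among the groups will be evaluated using a Chi-square test" or Fisher's exact test. No main effect or interaction is named.

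Under Secondary outcomes, "Skindex 29 will be checked at weeks 0 (baseline) and 4 (end of the trial"), and lesions are counted from photographs at the same two times. VAS and IGA are recorded at every session. IGA is scored 1 to 5.

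**The concern.** A factorial design is chosen so that the effect of each treatment and their interaction can be separated. The plan keeps that structure for the continuous outcomes and drops it for IGA. A significant four-group result would show that the arms differ somewhere. It would not show whether KRTE, acupuncture or the combination was responsible. The test also spreads its power over three degrees of freedom when the questions of interest have one each.

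The lesser matter is the repeated-measures ANCOVA for counts and Skindex-29. With only two time points, one of the two repeated values is the pre-randomisation baseline. The aim is worded as a difference over time rather than between arms. If baseline is not also a covariate, the time-by-factor term is a change-score analysis, which is less precise than the baseline-adjusted ANCOVA that the primary outcome receives.

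**Working it through.** **Inputs from the documents.** Four arms, and "The allocation ratio will be 1:1:1:1 in blocks of 4". On size, "the desired sample size for this pilot study is 44 patients, with 11 for each group, assuming a drop-out rate of 10"%. The 95% confidence level under Statistical analysis plan implies a two-sided alpha of 0.05. After 10% drop-out, 11 × 0.9 = 9.9, or about 10 per cell. The article gives no expected IGA rates, effect sizes or baseline-to-week-4 correlations, so those below are assumptions. It also gives no power figure for these outcomes to reproduce.

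**1. IGA: what the four-group test can see.** Take 11 per group in the order WL, AO, KO, KA.

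- Table A, responders 3, 3, 8, 8: KRTE works and acupuncture does nothing.
- Table B, responders 3, 8, 8, 3: each treatment works alone and the combination does not, a pure interaction.

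Both tables have 22 responders in 44, so the expected count is 5.5 in each of the eight cells. Every observed count differs from it by 2.5. Chi-square = 8 × 2.5²/5.5 = 8 × 1.136 = 9.09 on 3 df, p = 0.028, for both. Fisher's exact test on the four groups also gives the two tables the same p-value, because relabelling the arms does not change it.

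The factorial contrasts do tell them apart. For KRTE, table A has 16/22 against 6/22: chi-square = 4 × 5²/11 = 9.09 on 1 df, p = 0.0026. Table B has 11/22 against 11/22: chi-square 0. For acupuncture, both tables have 11/22 against 11/22. The whole signal is therefore a KRTE effect in A and an interaction in B. This step needs no assumed effect size.

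**2. IGA: power.** Simulated, 10 per cell, order WL/KO/AO/KA:

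| Assumed improvement (%) | Four-group chi-square | Stratified (CMH) test of KRTE, uncorrected |
|---|---|---|
| 20/60/20/60 (KRTE only) | about 57% | about 74% |
| 30/30/70/70 (acupuncture only) | about 56% | about 5% |
| 30/70/70/30 (pure interaction) | about 56% | about 2 to 3% |
| 20/20/20/70 (synergy) | about 69% | about 43% |

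In the first row the CMH test falls to about 62% with continuity correction, and the exact stratified test has about 64%. In the last row the exact test has about 30%.

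At 11 per group, the uncorrected 1-df test that pools over the other factor gives a similar picture for a pure KRTE effect:

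- 30% against 60%: 0.34 (four-group) and 0.51 (1 df).
- 20% against 60%: 0.63 and 0.78.
- 30% against 70%: 0.61 and 0.79.

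The difference is 15 to 18 percentage points.

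**3. Counts and Skindex-29.** With two time points and baseline as a covariate, the time-by-KRTE term equals the ANCOVA of the week-4 value. In one simulated dataset of 44, both gave b = 0.8151, t = 3.4738, p = 0.00127. Without the covariate, the term is the change-score contrast. Its variance relative to ANCOVA is 2(1−r)/(1−r²) = 2/(1+r), where r is the baseline-to-week-4 correlation:

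- r = 0.3: 2/1.3 = 1.54.
- r = 0.5: 2/1.5 = 1.33.
- r = 0.7: 2/1.7 = 1.18.

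For an assumed KRTE effect of 0.8 SD at 11 per cell and r = 0.3, 0.5, 0.7, ANCOVA has power 0.76, 0.84, 0.95 and the unadjusted time-by-KRTE term 0.60, 0.73, 0.92. Both have a mean estimate of 0.80, so neither is biased.

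**The case against.** **On IGA.** This is one secondary endpoint of a 44-patient pilot, and the improved/not-improved split is prespecified. Keeping that split is largely a matter of preference; an ordinal model with 11 per cell and five categories is not clearly more reliable. The gain in power also depends on the version of the test: about 17 points for the uncorrected CMH test, but only 5 to 7 for the corrected or exact forms (an exact four-group test would lose some power too). Most importantly, factor tests alone could be worse for this trial. Under a pure interaction the four-group test is significant in about 56% of trials and the KRTE test in 2 to 3%; under synergy the figures are 69% and 43%. All of this stands. It governs the form of the fix, but it does not rescue a test that cannot attribute its result to either treatment.

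**On the continuous outcomes.** A reader might infer that the secondary tests do not estimate the randomised effects. The documents do not support that. The time-by-factor term is unbiased, and the factorial reporting rule follows these analyses. The method is called an ANCOVA and the preceding sentence controls for baseline, so baseline may well be a covariate here too. A halved effect (mean estimate 0.40 for a true 0.80) arises only if the between-subject term without baseline adjustment is reported. Regression to the mean matters only if the time effect is read as efficacy. The article states neither.

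Nor is every secondary endpoint affected. Percentage change in non-inflammatory lesions already receives a baseline-adjusted two-way ANCOVA, and VAS has more than two time points.

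**Conclusion.** The IGA point holds. The test named in the article cannot separate a KRTE effect, an acupuncture effect and an interaction, as the two tables with identical chi-square 9.09 show without any assumption about effect size. The loss of power is secondary and rests on assumed rates: at 20/60/20/60% with 10 per cell, about 57% against 74% (uncorrected) or 62 to 64% (corrected or exact).

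For lesion counts and Skindex-29 the point is one of precision only: a variance ratio of 1.54 to 1.18 for r from 0.3 to 0.7 if baseline is not a covariate, and no loss if it is. Neither point touches the primary analysis. Together they are a cheap improvement to a pilot's secondary analyses.

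**What to change.** **IGA.** Replace the four-group test with a model containing KRTE, acupuncture and KRTE × acupuncture. Use exact or penalised logistic regression if the improved/not-improved split is kept, or an ordinal model of the week-4 score adjusted for baseline IGA. Alternatively, use a stratified CMH test for each factor, stratified by the other, plus a test of homogeneity of the odds ratios. The interaction must be included in either form, because CMH tests alone would miss it. Report the improvement percentage in each of the four arms.

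**Lesion counts and Skindex-29.** Use a two-way ANCOVA of the week-4 value on baseline, KRTE, acupuncture and their interaction, in line with the primary analysis.

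**Cost.** Analysis wording only; all the data are already collected. The factor tests assume a similar effect at both levels of the other factor and lose power under synergy. The interaction test has little power at this size, so a non-significant interaction should not be read as evidence that there is none.

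### The reporting rule leaves either both efficacy hypotheses or the effects against waiting list without an inferential estimate, and the choice hangs on an interaction test that is underpowered at 10 to 11 per cell

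*Protocol article*

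**What the plan says.** The Objective section of the Protocol article lists three null hypotheses on the percentage change in inflammatory lesions: no KRTE-by-acupuncture interaction, no difference between the KRTE group and the waiting list, and no difference between the acupuncture group and the waiting list.

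Baseline data and Outcome data prescribes a two-way ANCOVA for percentage change and then a reporting rule in two branches: "If there is an interaction between KRTE and acupuncture, only the interaction will be shown" and "If not, the main effect of KRTE and acupuncture will be reanalyzed and presented". It gives no significance level for deciding which branch applies.

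Under Sample size, "the desired sample size for this pilot study is 44 patients, with 11 for each group", with 10% drop-out assumed. No effect size, SD or power is given, and the trial is called a pilot. Allocation is equal: "The allocation ratio will be 1:1:1:1 in blocks of 4".

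The Statistical analysis plan section sets a general framework: "Statistical analysis will be conducted on an intension-to-treat basis with a 95% confidence interval using SPSS version 12.0 for Windows". It adds last observation carried forward for drop-outs and display of continuous data as mean ± SD.

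**The concern.** The rule decides from the data which of the trial's own hypotheses receive an estimate.

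- **Interaction found.** Read as written, the second and third hypotheses get no inferential result, although both are stated objectives.
- **Interaction not found.** The factorial main effect of KRTE compares the two KRTE groups with the two groups without it. The Objective section words the hypothesis against the waiting list. The two quantities agree only when there is no interaction, so a non-significant test is being relied on to show that there is none.

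At stake is whether a reader, or the planners of the large trial for which this pilot is to judge feasibility, can find the effect of each treatment against waiting list and the interaction with its uncertainty, whatever the p-value.

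**Working it through.** **Inputs from the article.** 11 per group, 44 in total, equal allocation, 10% drop-out (Sample size; Randomization and blinding). Two-sided 5% is inferred from the 95% confidence interval; 10% is shown as a sensitivity.

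**Assumed here, not in the article.** An interaction of 1 residual SD as benchmark, with a range of 0.5 to 2 SD.

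**The plan's own figure.** 4 × 11 = 44, and 11 × 0.9 = 9.9, or about 10 completers per cell. There is no power calculation to reproduce. Intention-to-treat with carried-forward values supports n = 11 in the analysis; n = 10 is the completer count.

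**What each branch estimates.** Let a = KO − WL, b = AO − WL and g = KA − KO − AO + WL.

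- Main effect of KRTE = ½[(KO − WL) + (KA − AO)] = a + g/2.
- The hypothesis against waiting list concerns a. The two differ by g/2.
- Example: a = b = 0.8 SD and the combination adds nothing, so KA − WL = 0.8. Then g = 0.8 − 0.8 − 0.8 = −0.8, and the main effect is 0.8 − 0.4 = 0.40 SD, half the stand-alone effect.

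**Precision (residual SD = 1).** SE is √(4/n) for the interaction, √(2/n) for a simple effect and √(1/n) for a main effect. The critical t is 2.021 on 40 df (n = 11) and 2.028 on 36 df (n = 10).

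| Contrast | SE, n = 11 / 10 | 95% CI half-width, n = 11 / 10 |
|---|---|---|
| Interaction | 0.603 / 0.632 | 1.22 / 1.28 |
| Simple effect | 0.426 / 0.447 | 0.86 / 0.91 |
| Main effect | 0.302 / 0.316 | 0.61 / 0.64 |

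**Power of the interaction test** (non-central t with non-centrality g/SE; for g = 1, 1/0.603 = 1.66 at n = 11 and 1/0.632 = 1.58 at n = 10).

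| True interaction | Power at 5%, n = 11 / 10 |
|---|---|
| 0.5 SD | 12.8% / 12.0% |
| 0.8 SD | 25.4% / 23.4% |
| 1 SD | 36.7% / 33.7% |
| 1.5 SD | 68.0% / 63.6% |
| 2 SD | 89.9% / 86.8% |

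A 1-SD interaction is therefore missed in 63% (n = 11) to 66% (n = 10) of trials. At a 10% level power is 49.5% / 46.3%, so it is missed in 51–54%. If 1 SD means the raw SD and baseline correlates 0.5 with outcome, power at 5% is 46% / 43% and the miss rate 54–57%. Power of 80% needs an interaction of 1.73 SD (n = 11) or 1.82 SD (n = 10). Spending one degree of freedom on baseline changes power by no more than about 0.1 percentage point.

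**Does the pre-test itself bias the main effect?** With cells ordered WL, KO, AO, KA, the main-effect weights are (−½, +½, −½, +½) and the interaction weights (+1, −1, −1, +1). The sum of products is −½ − ½ + ½ + ½ = 0, so in a balanced design the contrasts are orthogonal. Simulating the two-stage rule (200,000 trials per scenario) agrees: at n = 11 with a = b = 1 and g = −1, the mean main effect among trials with a non-significant interaction is 0.499, against a + g/2 = 0.50. Its nominal 95% interval covers the effect against waiting list in 65% of those trials, because it is centred on a different quantity.

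**The case against.** Several points on the other side stand.

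- **Pilot status.** The trial need not be powered for an interaction, and low power is not in itself a defect here. Declining to interpret main effects when an interaction is present is also common factorial practice. What remains is that a low-powered test should not decide which stated hypotheses get an estimate.
- **A reader might infer that one branch suppresses all efficacy results.** The article does not support this. The display of means ± SD is stated outside the conditional rule, and the comparison of IGA improvement among the groups is not conditional on the interaction. Group summaries may well appear in either branch. That display does not, however, promise adjusted means or contrasts against the waiting list with intervals.
- **A reader might infer that the pre-test biases the main effects.** It does not, as the orthogonality shows. The 0.40 SD in the example is the marginal effect by definition, and a correctly labelled main effect from the full model would give the same value.
- **A reader might call the test near-uninformative.** That is too strong when power is 87–90% at 2 SD. Underpowered for moderate interactions is the accurate description.
- **Wording.** The article says the main effects are reanalysed. That the interaction term is dropped, and that p > 0.05 decides, are natural readings but are not stated. Dropping the term would not change the estimate in a balanced design.

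**Conclusion.** The point holds as a flaw in a stated reporting rule for the primary-outcome analysis. In one branch, two of the three hypotheses in the Objective section get no inferential estimate, and this is true at any power. In the other, the effects shown differ from the effects against waiting list by half the true interaction, and the test cannot rule out an interaction of relevant size: its 95% interval extends about 1.2 to 1.3 SD either side of the estimate.

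The miss rates of 63–66% at 5% and 51–54% at 10% rest on an assumed interaction of 1 residual SD and assumed significance levels; the article states neither. The structural conflict between the rule and the hypotheses does not depend on those assumptions. The defect lies in reporting and estimand, not in the design, the data or the sample size.

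**What to change.** Replace the two-branch rule with one pre-specified model containing KRTE, acupuncture, KRTE × acupuncture and baseline. Whatever the interaction p-value, report from it:

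- the four adjusted cell means;
- the interaction with its 95% confidence interval;
- the simple effects KO − WL and AO − WL, which match the second and third hypotheses, and KA − WL, each with a 95% confidence interval;
- both main effects with 95% confidence intervals, labelled as marginal, that is, averaged over the other factor.

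State that a non-significant interaction will not be read as absence of interaction.

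The cost is two sentences in the analysis section and one more table; no extra patients or data are needed. The price in precision is visible and should be accepted: simple effects have intervals √2 times as wide as main effects (about 0.86 against 0.61 SD half-width at 11 per cell).

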#### Compliance

KRTE remaining after each session will be quantified in order to enhance medication compliance. Participants whose compliance with KTRE is ≤ 80% of the total dose or who receive fewer than six acupuncture sessions will be considered to have dropped-out.

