### Intervention

#### KRTE

KRTE is approved by the Korea Food and Drug Administration as a prescription in clinical practice for patients with sinusitis, otitis media, and acne. The components of KRTE are presented in Table 1. The authors purchased KRTE from the Han Kook Sin Yak Pharm. Co., which is equipped with a Korean good manufacturing practice (KGMP) facility. Participants in the KO and KA groups will be prescribed KRTE three times a day at a dose of 7.4 g after meals for 4 weeks.

**Table 1 T1:** Components of KRTE (7.4 g/dose)

Scientific Name	Amount (g)
*Schizoneptae Herba*	0.27
*Forsythiae Fructus*	0.34
*Ledebouriellae Radix*	0.65
*Angelicae gigantis Radix*	0.70
*Cnidii Rhizoma*	0.65
*Paeoniae Radix*	0.32
*Bupleuri Radix*	0.59
*Aurantii Fructus*	0.86
*Scutellariae Radix*	0.67
*Gardeniae Fructus*	0.89
*Angelicae dahuricae Radix*	0.35
*Platycodi Radix*	0.51
*Glycyrrhizae Radix*	0.67
**Total**	**7.40**

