#### Acupuncture

Certified acupuncture practitioners who have a minimum of 3 years of clinical experience obtained after a 6-year oriental medical college course will perform the acupuncture treatment. They will take a one-day training course for this trial. This course will include the study protocol, methods for acupuncture treatment, and basic information on clinical research. Eight sessions of acupuncture treatment will be performed twice per week for four weeks in patients who will be assigned to the AO and KA groups. Patients will receive acupuncture treatment at 11 classical acupuncture points and/or *ah shi *points that were randomly selected at papules and nodules on the face by the acupuncture practitioner. The following 11 acupuncture points will receive bilateral treatment: ST2 (*Sibai*), ST6 (*Jiache*), ST36 (*Zusanli*), LI20 (*Yingxiang*), LI11 (*Quchi*), PC6 (*Neiguan*), HT8 (*Shaofu*), SP3 (*Taibai*), SP6 (*Sanyinjiao*), SP10 (*Xuehai*), and LR3 (*Taichong*). These points will be treated with 0.25 × 30 mm disposable acupuncture needles (Dongbang Co., Korea). Selection of these acupuncture points was based on a literature review and previous studies of acupuncture treatment of acne vulgaris [20,21] and from the attending doctor's clinical experience and they will be located according to WHO standard Acupuncture Point Locations in the Western Pacific Region [32]. Patients will remain in a supine position for 15 minutes during acupuncture treatment. Papules and nodules will not be artificially extruded.

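### Counting non-adherence as drop-out gives the arms different drop-out definitions and leaves open whether non-adherers' week-4 lesion counts are used

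*Protocol article*

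**What the plan says.** The analysis principle, under Statistical analysis plan, is: "Statistical analysis will be conducted on an intension-to-treat basis". The same paragraph adds: "Missing values of drop-out participants will be imputed by the last observation carried forward (LOCF) method".

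The Compliance section then sets two conditions for being a drop-out. One covers "Participants whose compliance with KTRE is ≤ 80% of the total dose". The other covers those "who receive fewer than six acupuncture sessions will be considered to have dropped-out".

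The treatments that these conditions refer to are not given to every arm. For KRTE: "Participants in the KO and KA groups will be prescribed KRTE three times a day". For acupuncture: "Eight sessions of acupuncture treatment will be performed twice per week for four weeks in patients who will be assigned to the AO and KA". The waiting list (WL) receives neither during the four weeks.

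Under Baseline data and Outcome data the article lists what will be reported and compared between groups: "Proportion of drop-outs and compliance with KRTE and questionnaire completion will be calculated". Under Secondary outcomes, lesions are counted from photographs at weeks 0 and 4 only. The Objective section makes the KRTE-by-acupuncture interaction on the primary outcome the first null hypothesis, and names feasibility of a large trial as an aim.

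**The concern.** Loss to follow-up and poor adherence are different events, and the article puts both under one label. Two things follow.

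First, the label means different things by arm. In WL a drop-out can only be someone lost or withdrawn. In KRTE-only (KO) and acupuncture-only (AO) it is that or failing one adherence threshold. In the combination arm (KA) it is that or failing either of two. A between-group test of drop-out percentages then partly compares definitions, and this is a result that the larger trial would be planned from.

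Second, the same label names the group to which LOCF applies. With no lesion count between weeks 0 and 4, LOCF on the primary outcome can only carry the baseline count forward, which is a change of 0%. If a non-adherer is withdrawn, or has a week-4 count that is not used, that person is scored as unchanged because of behaviour after randomisation, in treated arms only. That would bear on both main effects and on the interaction test.

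**Working it through.** **Who can meet the triggers.** WL: none. KO: one (KRTE). AO: one (sessions). KA: two. Read literally, everyone in WL and KO receives zero sessions, so 11 + 11 = 22 of 44 would be drop-outs. That cannot be intended, so the rule has to be read as applying to assigned treatment only.

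**The plan's own figure.** Sample size gives 44 patients, 11 per group, with 10% drop-out; 11 × 0.9 = 9.9 per group. No number before inflation and no adherence rate is given. I take the 10% as ordinary loss, equal in all arms. The article does not say whether it also covers non-adherence.

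**Assumptions, none from the documents:** true mean changes of −10 (WL), −35 (KO), −35 (AO) and −60% (KA), so the KRTE main effect is −25 and the interaction is 0; non-adherence q = 10% (20%) for each assigned component; every non-adherer imputed as 0% change; non-adherers otherwise respond like the rest of their arm.

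**Formulas.** With d = 0.10:
- WL share = d; KO and AO share = 1 − (1 − d)(1 − q)
- KA share = 1 − (1 − d)(1 − q)² if the two kinds of non-adherence are independent, or 1 − (1 − d)(1 − q) if they fully overlap
- analysed mean = true mean × (1 − share)
- KRTE main effect = ½[(KO + KA) − (WL + AO)]; interaction = KA − KO − AO + WL

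**Ordinary drop-out alone.** Means −9, −31.5, −31.5, −54. Main effect = ½[(−85.5) − (−40.5)] = −22.5, a loss of 2.5. Interaction = −54 + 63 − 9 = 0.

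**Adding the adherence rule:**

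| | q = 10% | q = 20% |
|---|---|---|
| WL share, mean | 10%, −9 | 10%, −9 |
| KO and AO share, mean | 19%, −28.35 | 28%, −25.2 |
| KA share, mean (independent) | 27.1%, −43.74 | 42.4%, −34.56 |
| KA share, mean (full overlap) | 19%, −48.6 | 28%, −43.2 |
| Main effect, independent | ½(−72.09 + 37.35) = −17.37 | ½(−59.76 + 34.2) = −12.78 |
| Loss beyond −22.5, independent | 5.1 | 9.7 |
| Main effect, full overlap | ½(−76.95 + 37.35) = −19.8 | ½(−68.4 + 34.2) = −17.1 |
| Loss beyond −22.5, full overlap | 2.7 | 5.4 |
| Interaction, independent | −43.74 + 56.7 − 9 = +3.96 | −34.56 + 50.4 − 9 = +6.84 |
| Interaction, full overlap | −48.6 + 56.7 − 9 = −0.9 | −43.2 + 50.4 − 9 = −1.8 |

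The acupuncture main effect behaves identically, because KO and AO were given the same assumed mean.

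**The drop-out comparison, with no LOCF assumption.** The share rows are also the drop-out percentages that would be reported. With the same 10% true loss everywhere, WL would show 10%, KO and AO 19% (28%), and KA between 19% (28%) with full overlap and 27.1% (42.4%) with independence.

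**The case against.** The strongest counter-case is that the two sections can be read consistently. LOCF is stated for missing values, and a non-adherer who is photographed at week 4 has none. Photographs are described for each patient, without an exception for non-adherers. The Compliance section mentions neither the analysis set nor imputation, and LOCF keeps drop-outs in their randomised arms. A reader might infer that the plan discards observed week-4 data, and so flatly contradicts intention-to-treat. The text does not support that: the conflict is definite only if non-adherers are withdrawn or their counts are not used. The full protocol or an SAP, not shown, may settle it.

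Three further inferences also go too far:

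- *Compliance-defined drop-out will be most frequent in KA.* KA has the most triggers, but no rates are given. With equal component rates and full overlap, KA equals KO and AO.
- *The rule creates a false interaction.* The positive shift depends on independence and on large additive effects. Full overlap reverses the sign. With a −10% change in all four arms, independence and q = 10%, the shift is −7.29 + 8.1 + 8.1 − 9 = −0.09.
- *The whole fall from −25 to −17.4 (−12.8) is due to the rule.* Of that, 2.5 points come from ordinary drop-out under LOCF and would remain after the fix.

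Scale matters too. With an assumed SD of 20 to 40 points, the interaction's standard error is 2 × SD/√11, about 12 to 24 points, so +4.0 is roughly 0.17 to 0.33 standard errors.

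Finally, KRTE compliance is listed for reporting alongside drop-outs, so part of the mixture could be separated. Acupuncture attendance is not listed there. The objection therefore limits the imputation point, but the unequal drop-out definitions remain.

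**Conclusion.** The point stands as a should-fix. On any sensible reading of the Compliance section, the planned drop-out comparison uses a different definition in WL, in KO and AO, and in KA, so it is not a like-for-like feasibility result. That conclusion needs no assumption about imputation.

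The effect on the primary analysis is conditional. If all non-adherers were imputed, the illustration gives a further loss in the KRTE main effect of 5.1 (9.7) points under independence or 2.7 (5.4) under full overlap. The interaction shift is +4.0 (+6.8) or −0.9 (−1.8) respectively. Effects, adherence rates and overlap are all assumed. The losses would be smaller if non-adherers truly respond less, and the rule would add none if their observed counts are analysed. What can be said firmly is that the label leaves that choice open, possibly until after the data are seen, in a trial with 11 per arm.

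**What to change.** 1. Remove the statement that non-adherers count as drop-outs. Define a drop-out as a randomised participant with no week-4 assessment, identically in all four arms.
2. State that every randomised participant is to be photographed and assessed at week 4, and that the observed value is analysed in the randomised arm whatever the adherence.
3. Report drop-out by arm, and separately report adherence to each assigned component: KRTE in KO and KA, acupuncture sessions in AO and KA.
4. Keep the 80% and six-session thresholds for adherence reporting and for a secondary per-protocol set, applied only to assigned treatment.

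This is a change of wording and the sample size stays at 44. It removes any distortion that comes from the adherence rule, but not the 2.5 points that ordinary drop-out under LOCF costs in the illustration. The downside is that the intention-to-treat estimate will include poorly adherent participants.
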